
#### 2.4.7. Assessment of Carotid Arteries Intima-Media Thickness

The carotid arteries intima-media thickness assessment takes place with the participant lying down in a dorsal position. Then, the following parameters are evaluated using a sphygmomanometer from Riester (Model RI-championN^®^, Jungingen, Germany): heart rate (HR), systolic blood pressure (SP) and diastolic blood pressure (DP). The intima-media thickness of the right and left carotid arteries are measured with a Doppler two-dimensional ultrasound and are assessed with the AIRC study protocol [33]. The following values are then recorded through a portable ultrasound from General Electric^®^ (VIDe, Vancouver, Canada) with probe linear 11 L: Intima-media thickness (IMT); systolic diameter (SD), diastolic diameter (DD), peak systolic velocity (PSV) and end-diastolic velocity (EDV).

#### 2.4.8. Heart Rate Variability (HRV) Measurement

HRV will be assessed according to the procedures of Abad et al. [34] using Polar V800 heart rate monitors. Participants will place the sensor, which is synchronized with the V800 clock, on their chest beneath their pectoral muscles. Then, the participants will be asked to lie down in a dorsal position, in silence, with open eyes and with a calm respiration. The test will have a duration of 10 min in a calm, silent and low-light environment. After the conclusion of the test, HRV measurement data are downloaded from the Polar Flow Web Service.

#### 2.4.9. Biochemical Markers

Blood samples will be drawn via venipuncture from fasting participants. For each participant a total of 18.5 mL of blood will be drawn. Of the 18.5 mL, 3.5 mL will be used by the clinic to assess lipid panel values (HDL, LDL, glucose, triglycerides). The remaining 15 mL, processed by the college laboratory, will be divided into three tubes: two serum separator tubes and one ethylenediaminetetraacetic acid (EDTA) tube. Once the test tubes arrive at the university laboratory a complete blood count (CBC) will be conducted using an automatic hematology analyzer Coulter Act Diff, Beckman Coulter, USA. Next, the test tubes are centrifuged for10 min at 3500× *g* rotations per minute and stored in cryogenic test tubes. Levels of HbA1C, IL-1, IL-1ra, IL-6, IL-10, TNF-alpha, Adiponectin, Leptin, MIP-1alpha, MCP-1, SOD, MMP-9, are subsequently analyzed with ELISA Invitrogen^®^ CA kits (Bender MedSystems GmbH, Vienna, Austria).

### 2.5. Ethical Aspects

The researcher will be responsible for the data integrity and validity during the entire study. All data collected will be confidential and used exclusively for scientific purposes. Anonymization procedures will be conducted under the Data Protection Regulation of 25 May 2018. Data anonymization will be implemented by attributing a code to each participant. Each participant will receive a unique identification code that will correspond to their process; this code will be visually accessible with the use of “code cards”. These “code cards” will be used by the participants during data collection. Once the data collection is finalized the participants will be asked to destroy their “code cards”, thus finalizing the anonymization process.

Data will be stored in an Excel Microsoft Office 2016 database. Access to this database will be protected with a password and will be restricted to the main researcher responsible for the data collection. Data backups will be carried out regularly by the main researcher.

Participation in this study is purely voluntary, with no reprisals for non-participation. All subjects will be asked for their informed consent before they start participating in the study. The study will be conducted in accordance with the Declaration of Helsinki, and the protocol was approved by the Ethics Committee for Health of the Faculty of Sport Sciences and Physical Education of the University of Coimbra (reference: CE/FCDEF-UC/00462019).

The results from this study will be disseminated through publication in various scientific journals. The participants, if desired, will receive a copy of the main results and publications.

### 2.6. Statistical Analysis

The size and statistical power of the sample will be calculated using the G*Power software application [35]. The following parameters will be considered: F test (ANOVA); effect size: 0.25; α-level: 0.05; statistical power: 0.95; number of groups: 4; number of measures: 2 (pré and post intervention); a 30% margin for possible losses and refusals. Therefore, the initial size of the total sample was estimated at 76 participants.

The collected data will be subjected to descriptive statistical analysis where values such as maximum, minimum, mean and standard deviation will be calculated for each variable in each assessment moment. Afterwards, data normality will be tested by considering the response to three conditions: z-values from Skewness and Kurtosis tests; *p*-value from Shapiro-Wilk test; and visual inspection of generated histograms. Parametric data will be analyzed using the Student’s *t*-test for independent samples to compare the groups and two paired samples to compare the different moments (M1 and M2). Nonparametric data will be analyzed using the Mann–Whitney U test to compare the groups and the Wilcoxon test to compare the different moments (M1 and M2). Statistical analysis will be performed using the Statistical Package for the Social Sciences (SPSS) statistical software, version 25.0. The level of significance used will be *p* ≤ 0.05.

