## 3. Expected Results/Discussion

The main aim of this study is to assess the impact of different aquatic exercise programs (a continuous aerobic program, aerobic interval program and combined program) on risk markers of cardiometabolic diseases in older people. The study is guided by scientific-based evidence on the practice of physical exercise in the elderly population [11,36].

The practice of regular physical exercise is considered as the optimum tool in the prevention and treatment of various types of cardiometabolic diseases. Thus, it is important that research on this topic continues; by doing so, new intervention methods can be identified and their efficacy validated. The offer of aquatic physical exercise programs is highly successful among the elderly because they transform physical exercise into something more pleasant and suitable for this particular population. However, the high costs of maintaining aquatic environments and the additional difficulties associated with assessment methodologies and specific equipment needed to monitor exercise in aquatic environments, means this topic not yet been sufficiently explored in the literature.

After completion of the data collection and analysis, the participants in the experimental groups are expected to show positive developments with regard to the anthropometric level, physical function, the intima-media thickness of the carotid arteries, heart rate variability, cognitive function, mental health and a number of biochemical markers. It is also expected that statistically significant differences will be found between the exercise groups for some of the variables. In the control group, no changes are expected in the analyzed variables. It is believed that the expected results can be attributed to the physical and physiological effects of the aquatic environment associated with the different proposed exercise protocols. The results will be published after the study is completed.

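### The stated power of 0.95 belongs to a four-group ANOVA F test that is not among the planned analyses, and the effect behind it is not given in interpretable units

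*Protocol article*

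**What the plan says.** Section 2.6 of the protocol article gives the inputs to the sample size calculation as "F test (ANOVA); effect size: 0.25; α-level: 0.05; statistical power: 0.95; number of groups: 4", with "number of measures: 2 (pré and post intervention") and "a 30% margin for possible losses and refusals". The result is 76 participants in total. The section does not say which ANOVA F test was used or what correlation between the two measures was assumed.

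The next paragraph sets out the analysis. Parametric data get Student's t-test "for independent samples to compare the groups and two paired samples to compare the different moments (M1 and M2"). Non-parametric data get the Mann-Whitney test between groups and the Wilcoxon test between moments. "The level of significance used will be *p* ≤ 0.05". Neither an ANOVA nor a group-by-time test is listed.

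Section 3 adds that "It is also expected that statistically significant differences will be found between the exercise groups for some of the variables". Section 2.2 reports that 102 people agreed to take part.

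**The concern.** Stated power is useful only if it belongs to the test that will be reported and to an effect the reader can picture. Here the test used for sizing compares four groups at once over two time points, while the listed tests compare two groups, or two moments within one group. The effect is given as "effect size: 0.25" with no translation into a difference between groups. A reader who takes 0.25 for a moderate effect would credit the study with more sensitivity than it has.

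The comparison between programmes is where this matters, since Section 3 expects differences there. If such a comparison shows no difference, the only power figure on the page is 0.95, and the result could be read as firmer than it is.

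**Working it through.** **Inputs from Section 2.6:** f = 0.25, alpha = 0.05, power 0.95, k = 4 groups, m = 2 measures, 30% margin, N = 76. **From Section 2.2:** 102 agreed. **Assumed:** equal groups (19 each at 76, about 25 each at 102), and the correlation rho between M1 and M2, which is varied below.

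**1. Reproducing 76.** For the group-by-time interaction, lambda = N·f²·m/(1 − rho), with df1 = (k − 1)(m − 1) = 3 and df2 = N − 4. At rho = 0.5:
- N = 72: lambda = 72 × 0.0625 × 2/0.5 = 18.0, power 0.948.
- N = 76: lambda = 76 × 0.0625 × 2/0.5 = 19.0, power 0.959.

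So 76 is the smallest equal-group total that reaches 0.95, before any dropout margin.

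**2. Other routes to 76.**
- The within-factor F test (df1 = 1) at rho = 0.3 also gives 76 (power 0.953). It tests the pooled change over time, not differences between groups.
- The interaction test at rho = 0.65 needs 53 completers (power 0.953), and 53/0.7 = 75.7, rounded up to 76. This route does include the 30% margin.

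The first set-up is the likeliest, but the text does not establish it.

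**3. What f = 0.25 means in the interaction test.** With two time points, each group's interaction effect is plus or minus half the deviation of its mean change from the average change. Hence the SD of the four mean changes is 2·f·sigma = 0.5 outcome SD, whatever rho is. The largest difference D between groups is then:

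| Pattern of the four mean changes | SD of means | D |
|---|---|---|
| Two groups v two | D × 0.5 | 1.00 SD |
| Three equal programmes v control | D × √(3/16) | 0.5/0.433 = 1.15 SD |
| Equally spaced | D × √5/6 | 0.5/0.373 = 1.34 SD |
| Two extremes, two midway | D × √(1/8) | 0.5/0.354 = 1.41 SD |

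**4. Power of the planned two-group t test.** Two-sided 0.05, noncentral t with noncentrality d·√(n/2) and 2n − 2 df. For example, n = 19 and d = 0.5 give 0.5 × √9.5 = 1.54 against a critical value of 2.03, power 0.32.

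| Difference (assumed) | 19 per group | 25 per group |
|---|---|---|
| 0.5 SD | 0.32 | 0.41 |
| 0.8 SD | 0.67 | 0.79 |
| 1.155 SD | 0.93 | 0.98 |
| Difference giving power 0.95 | about 1.20 SD | about 1.04 SD |

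These figures apply to post-intervention values, and equally to change scores at rho = 0.5, where the SD of change, sigma·√(2(1 − rho)), equals the outcome SD. At rho = 0.7 a change-score t test for 0.5 outcome SD has power 0.49 with 19 per group and 0.61 with 25.

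**5. Power of the planned paired t test** with 19 in a group: 0.54 at a standardised mean change of 0.5, and 0.91 at 0.8.

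**6. Sensitivity of the omnibus interaction test** to the unstated correlation, at N = 76 and f = 0.25: 0.87 at rho = 0.3, 0.96 at 0.5 and 0.998 at 0.7. At N = 102 and rho = 0.3 it is 0.954.

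**The case against.** Four points can be made for the plan.

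- **The change of test costs little at the sized effect.** At 1.155 SD the two-group t test has 0.93 with 19 per group and 0.98 with 25, and at 1.41 SD about 0.99 or more. This stands. The low figures above come mainly from the smaller assumed difference, not from replacing the F test by a t test.
- **No smaller effect is named as the target.** A reader might infer that 0.5 SD is the realistic effect and that the trial therefore has about a third of its stated power. The article gives no expected difference in SD units, so 0.5 to 0.8 SD is an assumption and belongs in a range. At 25 per group and 0.8 SD the power is 0.79.
- **The set-up behind 76 is not certain.** A reader might infer that only the interaction test at correlation 0.5 gives 76, or that the arithmetic is wrong. Neither follows: other set-ups also give 76, and the figure can be reproduced.
- **The article makes no claim of 95% power for a null comparison between programmes.** True. The risk lies in how the single power figure would be read.

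It could also be said that details are left to a fuller analysis plan. That does not answer the point, because this section itself fixes both the sizing test and the list of analyses, and the two differ.

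**Conclusion.** The point holds as a mismatch between sizing and analysis. The figure "statistical power: 0.95" belongs to a four-group F test that the plan does not list, and it is not the power of the tests that are listed. This conclusion rests on the text alone.

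The size of the gap rests on assumptions: equal groups, a two-sided test, and a difference chosen by the reader. Within 0.5 to 0.8 SD, the two-group t test has power 0.32 to 0.67 with 19 per group and 0.41 to 0.79 with 25. It matches the stated power only from about 1.2 SD and 1.04 SD respectively. The reading of f = 0.25 as 1.0 to 1.4 SD depends on the F test being the interaction, but not on the correlation. That the correlation was 0.5 and that no margin was applied are the likeliest inferences, not facts. The mismatch should be corrected, but it does not show that the trial is too small, since no target difference is given against which to judge that.

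**What to change.** In Section 2.6:

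1. Make the four-group group-by-time model, or a baseline-adjusted four-group model, the main test, with pairwise comparisons following it.
2. State which F test and which correlation were actually used in the calculation. The authors should report their own input, not adopt 0.5 because it reproduces 76.
3. Express f = 0.25 as a difference in SD units for a named pattern. If the interaction test was used, this is about 1.15 SD for three equal programmes against control.
4. Replace the bare 0.95 with the power, or the detectable difference, of the test to be reported at the expected number of completers.

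The cost is a rewrite of one section and a less favourable stated power. No extra participants or data are needed for this alignment. It does not raise power for smaller differences; it only lets readers see what the study can detect.

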### 2.2. Participants

The participants were recruited in the central area of Portugal, more specifically in the region of Sertã. The sample was recruited by the non-probabilistic method for convenience. One hundred and fifty individuals from the community were personally invited, but only 102 agreed to participate in the study (mean age of 72.32 ± 5.2 and BMI 29.47 ± 4.85). Participants will be selected according to the following inclusion criteria: individual of both genders; age equal to or above 65 years of age; non-institutionalized individuals; they give permission to be part of the study and if the participant presents with a clinical condition or comorbidity, it must be stable and enable participation in aquatic-based exercises classes as approved by local medical staff. The exclusion criteria are: individuals less than 65 years of age; individuals with medical diagnosed pathologies that jeopardize their health while preforming aquatic based exercises, participants that attend less than 50% of all the sessions and participants who cannot complete all of the proposed tests.

The participants will be distributed randomly into different exercise groups based on their registration for one of the schedules offered for the hydro-gymnastics sessions. There will be three distinct schedules (9.00, 9.50 and 10.40), with the constraint being that the participants must attend the same schedule for the whole year. The 9.00 session includes the continuous aerobic program, the 9.50 session includes the interval aerobic program, and the 10.40 session includes the combined exercise program. This information will not be provided to participants before they register for the sessions so it will not be possible to establish any association between the schedule and the different exercises programs. Such information will be communicated later in the study. The control group will be randomly recruited from the community and will include those individuals that have not been involved in any kind of physical exercise during the last year.

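### Name Welch's test for the group comparisons: group sizes are uncontrolled, and Student's t-test does not protect the 5% level if spreads also differ

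*Protocol article*

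**What the plan says.** Protocol article, section 2.6, gives the sizing inputs as "F test (ANOVA); effect size: 0.25", alpha 0.05, "statistical power: 0.95; number of groups: 4" and "number of measures: 2 (pré and post intervention", and concludes that "the initial size of the total sample was estimated at 76 participants". For the analysis it names Student's "test for independent samples to compare the groups" where data are judged normal, and the Mann-Whitney test otherwise. Normality is judged in three ways (skewness and kurtosis z-values, Shapiro-Wilk, histograms). Equality of variances is not mentioned.

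Section 2.2 places exercise participants "based on their registration for one of the schedules offered for the hydro-gymnastics sessions", at 9.00, 9.50 or 10.40. The control group is recruited from the community by a separate route. No quota, ratio or target size is given for any of the four groups. The section reports that 102 people agreed to participate.

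**The concern.** The pooled t-test tolerates unequal spread when the two groups are about equal in size. It loses that tolerance when they are not. Section 2.2 leaves the sizes to whoever registers for each hour and to a separate control recruitment. The exclusion of people attending under 50% of sessions can shrink only the exercise groups, and not necessarily evenly.

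Unequal spread is plausible. Section 3 expects improvement in the exercise groups and no change in controls, and people often respond to a programme to different degrees.

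Two things are at stake: the 5% level of each group comparison, which could be off in either direction, and the meaning of the stated 0.95, which depends on group sizes that the plan does not secure.

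**Working it through.** **1. The plan's own figure.** Inputs from section 2.6: f = 0.25, alpha = 0.05, k = 4 groups, m = 2 measures. Assumed, because not stated: correlation rho = 0.5 between the measures, and equal groups.

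For the group-by-time F test, lambda = N × m × f² / (1 − rho), with 3 and N − 4 degrees of freedom.

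- N = 76: lambda = 76 × 2 × 0.0625 / 0.5 = 19.0; power 0.959.
- N = 72: lambda = 18.0; power 0.948.

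So 76, or 19 per group, is the smallest multiple of four that reaches 0.95. The result depends on rho: 104 at 0.3 and 48 at 0.7. The other ANOVA variants tried at rho = 0.5 give 56, 212 and 280, so the interaction test with equal groups is the reading that reproduces 76. It does so before any allowance for losses.

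**2. Power when sizes differ.** Assumed pattern: the three programmes work alike and controls do not change. On change scores, lambda / N = 19 / 76 = 0.25. With equal groups this pattern has between-group variance (1/4)(3/4)d² = 0.1875d², so d² = 0.25 / 0.1875 = 4/3. Holding the means fixed, with c controls, lambda = (4/3) × c(N − c) / N.

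| N | Controls | lambda | Power |
|---|---|---|---|
| 76 | 19 | 19.0 | 0.959 |
| 76 | 10 (programmes 30/22/14) | 11.6 | 0.80 |
| 76 | 30 (programmes 22/14/10) | 24.2 | 0.99 |
| 102 | 25 or 26 | 25.5 | 0.99 |
| 102 | 12 | 14.1 | 0.89 |

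Under this pattern only the number of controls matters. If a single programme is the one that differs, the size of that programme takes its place.

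**3. Why the pooled test can go wrong.** Its squared standard error is s²(1/n1 + 1/n2), with s² = [(n1 − 1)s1² + (n2 − 1)s2²] / (n1 + n2 − 2). The correct squared standard error is s1²/n1 + s2²/n2. Take assumed sizes of 12 and 26, where 1/12 + 1/26 = 0.1218.

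- SD 2 in the 12 and 1 in the 26: s² = (11 × 4 + 25 × 1) / 36 = 1.917. Pooled SE = √(1.917 × 0.1218) = 0.483; correct SE = √(4/12 + 1/26) = 0.610; ratio 0.79. The test is too liberal.
- SD 1 in the 12 and 2 in the 26: s² = (11 × 1 + 25 × 4) / 36 = 3.083. Pooled SE = 0.613; correct SE = √(1/12 + 4/26) = 0.487; ratio 1.26. The test is too strict.

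**4. Resulting type I error.** Simulation of normal data with no true difference, two-sided 5%. All unequal sizes and all SD ratios are assumptions.

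| Sizes | SDs | Student | Welch |
|---|---|---|---|
| 19 v 19 | one group 2× | about 5.2% | about 5% |
| 12 v 26 | equal | about 5% | about 5% |
| 12 v 26 | smaller group 1.5× | about 9% | about 5% |
| 12 v 26 | smaller group 2× | about 12% | about 5% |
| 12 v 26 | larger group 1.5× | about 2.5% | about 5% |
| 12 v 26 | larger group 2× | about 1.6% | about 5% |

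**5. Price of Welch when SDs are in fact equal.** At an assumed true difference of 0.9 SD, power with 19 per group is 0.771 for Student and 0.769 for Welch. At 12 v 26 it is about 0.71 and 0.69.

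**The case against.** A reader might infer that the 5% level fails in this trial. The document does not support that. Unequal sizes alone leave Student's test at 5%, and the article gives neither group sizes nor SDs by group. The expectation that controls will not change concerns means and supplies no SD ratio. If exercisers do vary more and controls are the small group, the control comparisons fall in the conservative rows of the table: real differences are missed, but false positives do not rise. This part stands, and it makes the point conditional.

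A reader might also infer that imbalance must cost power. It need not: a large control group raises it. The 102 who agreed to participate are a cushion over 76, although 12 controls among 102 would still give 0.89.

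It can further be said that an article may leave variance handling to a fuller plan, that SPSS prints the unequal-variance result anyway, and that non-normal variables go to Mann-Whitney. The article does, however, name the test, and by that name it is the pooled one. With both results printed and neither chosen in advance, the choice between two p-values is left open. The Mann-Whitney branch limits the point to variables judged normal but does not remove it.

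Finally, the 0.95 describes a four-group F test and not the planned two-sample tests, even with equal groups. That is correct, and is a reason to say plainly what the 0.95 refers to.

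**Conclusion.** The concern holds as a conditional weakness with a cheap remedy. The plan combines uncontrolled group sizes with a test that is safe only if sizes or spreads are about equal, and it checks neither. If both differ, at 12 v 26 and a 1.5 to 2 times SD ratio, the true level lies anywhere from about 1.6% to about 12% depending on which group is more variable. Welch's test stays near 5% throughout. These sizes and ratios are illustrations and not forecasts.

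The 0.95 at N = 76 reproduces for an F test with four equal groups and a correlation of 0.5. At other sizes it can be lower or higher: 0.80 with 10 controls and 0.99 with 30, under the pattern in which the programmes work alike. The power is therefore not assured, but it is not shown to be lost either.

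**What to change.** 1. In section 2.6, name Welch's unequal-variance t-test in advance for every between-group comparison of a normally distributed variable, or robust standard errors if a model is used. SPSS already prints the result. The cost is about 0.1 percentage points of power with 19 per group, and about 2 points at 12 v 26 when the SDs are equal.
2. State that the 0.95 at N = 76 refers to a four-group F test with equal groups, give the correlation assumed, and report the power for the group sizes actually obtained from the 102 who agreed. This costs a sentence and a recalculation.
3. Optional, and only if registration is still open: give each class the same quota and recruit controls to the same number. Some late registrants would be offered another hour.

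### Three normality checks on the trial's own data, one of them visual, choose between mean-based and rank-based tests, and neither between-group test uses the M1 value

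*Protocol article*

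**What the plan says.** All of the inferential plan stands in section 2.6 of the protocol article. After descriptive summaries, "data normality will be tested by considering the response to three conditions". The conditions are "z-values from Skewness and Kurtosis tests", the Shapiro-Wilk p-value and "visual inspection of generated histograms".

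Variables judged normal go to Student's t "test for independent samples to compare the groups and two paired samples to compare the different moments (M1 and M2"). For the rest, "Nonparametric data will be analyzed using the Mann–Whitney U test to compare the groups and the Wilcoxon test to compare the different moments".

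Whichever route is taken, the maximum, minimum, "mean and standard deviation will be calculated for each variable in each assessment moment".

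The variables that pass through this choice include concentrations that are often skewed. Section 2.4.9 lists "Levels of HbA1C, IL-1, IL-1ra, IL-6, IL-10, TNF-alpha, Adiponectin, Leptin, MIP-1alpha, MCP-1, SOD, MMP-9", as well as triglycerides and other routine blood values.

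**The concern.** The t-test asks whether two means differ. The Mann-Whitney test asks whether values in one group tend to exceed those in the other. Letting the data choose between them leaves the question undetermined until the data are in. One of the three checks is a visual judgement, so two analysts who follow section 2.6 faithfully can reach different tests for the same marker.

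Three things are at stake:

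- A significance verdict can turn on the choice of test.
- The two routes have no common effect estimate with an interval, so inferential results do not line up across markers.
- On either route the between-group comparison uses two independent samples and discards the M1 measurement, which every participant is to provide. That costs power.

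The text also allows, without stating it, that the check is run within groups or separately at M1 and M2. If so, one marker could be tested under different hypotheses at different places in the same report.

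**Working it through.** **Inputs from the article.** Section 2.6: planned total 76, four groups, two moments, significance at 0.05. Section 2.2: 102 people agreed to take part. With an equal split, which is an assumption, 76/4 = 19 and 102/4 = 25.5, taken as 25.

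**Inputs assumed.** The article gives no SD or M1-M2 correlation for any marker. Skewed markers are taken as lognormal with log-SD 0.3 to 0.8, the correlation as 0.5 to 0.7, and the effect as 0.6 SD (on the log scale for skewed markers).

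**The plan's own figure.** The total of 76 reproduces as a group-by-time interaction F test with f = 0.25 and assumed correlation 0.5. The noncentrality is 0.25² × 76 × 2/(1 − 0.5) = 19.0 on 3 and 72 degrees of freedom, giving power 0.959. The smallest N is 73, or 76 in equal groups, before any allowance for losses. That allowance is a separate matter; 76 serves here only to set the group size.

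**1. How stable is the classification?** Share of lognormal samples flagged by Shapiro-Wilk alone at 0.05, approximate ranges over repeat simulations of 4,000 samples per setting:

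| Unit checked | log-SD 0.4 | log-SD 0.5 |
|---|---|---|
| One group, n = 19 | 35–37% | 49–50% |
| One group, n = 25 | 46–48% | 61–64% |
| Whole sample, n = 76 | 93–94% | 99% |
| Whole sample, n = 102 | 98% | over 99% |

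The result depends on the unit: unstable within groups, nearly fixed if the whole sample is checked once.

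**2. If the gate is applied at each moment.** Take two groups, correlation 0.5, and a t-test only if skewness and kurtosis have |z| < 1.96 and Shapiro-Wilk p > 0.05 in both groups. The between-group test then differs between M1 and M2 in about 28% of runs for exactly normal data, 46–48% at log-SD 0.3, 17–31% at 0.5 and 1–5% at 0.8. The numerical checks disagree with one another within a single group in 7–34% of samples. Histogram inspection cannot be simulated.

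**3. Type I error.** The two-stage between-group comparison rejects a true null in 0.041 to 0.061 of runs. The simulation standard error is √(0.05 × 0.95/4000) = 0.0034. Even taking the smaller of the two p-values gives only about 0.06.

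**4. Does the choice of test change the verdict?** Applied to identical data with a 0.6 SD shift, the t and Mann-Whitney tests fall on opposite sides of 0.05 in about 7% of comparisons for normal data and 10–13% for log-SD 0.4 to 0.5. Under the null they disagree in about 2–3%.

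**5. What ignoring M1 costs.** Adjusting for M1 multiplies the residual variance by 1 − ρ²: 0.75 at ρ = 0.5 and 0.51 at ρ = 0.7. A normal approximation for two groups of n has noncentrality 0.6 × √(n/2), divided by √(1 − ρ²) when adjusted:

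- n = 19, ρ = 0.5: unadjusted 1.849, power Φ(1.849 − 1.96) = 0.46; adjusted 1.849/0.866 = 2.135, power Φ(0.175) = 0.57.
- n = 25, ρ = 0.7: unadjusted 2.121, power Φ(0.161) = 0.56; adjusted 2.121/0.714 = 2.970, power Φ(1.01) = 0.84.

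Simulation without the approximation gives somewhat lower values: 0.39 to 0.55 for the planned two-sample tests against 0.48 to 0.81 for the baseline-adjusted model with robust standard errors. Each range spans both group sizes and both correlations, so the matched pairs above show the gain more clearly.

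**The case against.** Section 2.6 does not say that the decision is made by moment, by group or by pair of groups. The phrase about each moment belongs to the descriptive summaries. The wording fits one classification per variable equally well, and then no switching occurs. Cut-offs and a rule for conflicting checks are also details that a condensed article may leave to a fuller plan. Both points stand, so the switching rates in step 2 are conditional and the missing details are not the fault. What remains is the gate that the article does state.

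A reader might infer several stronger things that the documents do not support:

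- **That the gate is close to a coin toss for skewed markers.** This holds only for checks within groups of about 19 to 25 and for the assumed log-SDs. Equal groups are also an assumption.
- **That normal data would often be misrouted.** Across eight group-by-moment cells, 1 − 0.95⁸ = 0.337. That figure treats M1 and M2 from the same people as independent, uses Shapiro-Wilk alone and lets any single flag decide. Section 2.6 considers three conditions together.
- **That error rates are inflated.** Step 3 shows that they are not, to any material degree.
- **That the rank tests are to blame for ignoring baseline.** The Wilcoxon test compares M1 with M2 and so uses it, while the independent t-test ignores baseline just as the Mann-Whitney test does.
- **That effects could not be compared at all.** Means and SDs are planned for every variable at each moment, so a descriptive comparison remains possible.

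It can also be said that the verdict seldom changes and that fixing one test per variable would be enough. That would remove the discretion, but it would leave the power loss and the missing common estimate.

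**Conclusion.** The point holds in a limited form. A partly visual, data-driven check decides whether means or ranks are compared. Three costs follow: a discretionary choice that changes the significance verdict in about 7 to 13% of comparisons, no common inferential effect estimate, and between-group tests that leave the M1 value unused. Validity in the sense of type I error is not threatened. Testing one marker under different hypotheses at different moments or in different groups is possible under the text but not stated by it.

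The sizes rest on equal groups of 19 to 25, lognormal markers with log-SD 0.4 to 0.5 (or normal data), a 0.6 SD effect and, for the power gain, a correlation of 0.5 to 0.7. None of the last three comes from the article. The direction of the power result needs only a non-zero M1-M2 correlation of useful size.

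**What to change.** Replace the normality gate in section 2.6 with one pre-set analysis for each continuous outcome: a linear model of the M2 value on group (four levels) and the M1 value, with robust standard errors, reporting adjusted between-group differences and 95% confidence intervals.

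Fix the scale of each outcome before the data are examined: for example, log for cytokines, adipokines and triglycerides, with the M1 value on the same scale, and a stated scale for heart rate variability indices and for bounded scores such as MMSE and GDS. Keep the Mann-Whitney and Wilcoxon tests as a sensitivity analysis. Use histograms and normality plots as diagnostics that do not change the primary analysis.

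This changes analysis wording only. It needs no new measurement, because M1 is already collected, and no change in the planned number of participants. The downside is that log-scale results are read as ratios rather than differences. The model does not settle other questions about how the groups are formed.
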